### Participants

Participants were recruited via advertisements in local papers and the distribution of flyers at local churches, universities and community groups in Cape Town, SA. Participants were included if they met the following inclusion criteria: (1) black SA women (based on the Xhosa ancestry of both parents) between the ages of 20 and 35 years; (2) obese (body mass index (BMI) 30-40 kg/m^2^); (3) weight stable (weight not changed more than 5 kg or no change in clothes size over the past 6 months); (4) sedentary (not participating in exercise training (>1 session of >20 min per week) within the last 12 months); (5) on injectable contraceptive (depot medroxyprogesterone acetate, 400 mg) for a minimum of 2 months; (6) no known metabolic or inflammatory diseases; (7) no hypertension (≥140/90 mmHg), diabetes (random plasma glucose concentration of >11.1 mmoL/L, and/or hemoglobin A_1c_ (HbA_1c_) result >6.5% A_1c_), HIV, or anemia (hemoglobin (Hb) <12 g/dL); (8) not taking any medications; (9) nonsmokers; (10) not currently pregnant or lactating; (11) no orthopedic or medical problems that may prevent exercise participation; and (12) no surgical procedures within the last 6 months.

### Screening

Before participation in the trial, volunteers completed screening procedures. Weight and height were measured to calculate BMI. Blood pressure was measured 3 times at 1-min intervals using an automated blood pressure monitor (Omron 711, Omron Health Care, Hamburg, Germany). A venous blood sample was drawn for the determination of glucose, Hb and HbA1_c_. HIV screening was performed and participants were excluded based on a confirmed positive test or if they refused to complete the test.

**Figure 1 figure1:**
[figure not shown]
Consort diagram outlining participant enrollment, allocation, follow-up, and analysis. BMI: body mass index.

Participants received pre- and posttest counseling from a trained counselor, and a referral was made to appropriate HIV clinics for those participants who were found to be HIV-positive. Participants completed the physical activity readiness questionnaire (PARQ) [33] and were excluded if they answered “yes” to any of the questions. In addition, the participants completed a questionnaire about their exercise training, contraceptive use, ancestry, smoking status and history, medication use, and clinical conditions.

### Overview of Testing Procedures

The study design and stepwise stages of the protocol are described in Figure 2. Before and following the 12-week intervention, participants completed 4 data collection sessions. At the first session, participants completed a cardiorespiratory fitness test of peak oxygen consumption (VO_2peak_), and body composition was measured by dual energy x-ray absorptiometry (DXA). At least 72 hours later, the participants spent a night at the laboratory where they were given a standardized evening meal at 8 PM and then required to fast overnight (10 hours). During the evening or early morning, participants were requested to provide a fecal sample. At 6 AM, the participants completed measures of resting metabolic rate (RMR) and substrate metabolism, and resting heart rate and blood pressure were measured. At 7 AM, fasting blood samples were collected and participants underwent a frequently sampled intravenous glucose tolerance test (FSIGT). During the FSIGT, the field worker administered the questionnaires, and the participants completed a 24-hour dietary recall and food frequency questionnaire with a Health Professions Council of South Africa registered dietician. The participants were then requested to complete a 3-day food diary. On a separate day, after a 10- to 12-hour overnight fast, participants completed steady-state exercise testing at 50% VO_2peak_. Thereafter, participants were provided a standardized meal and underwent a magnetic resonance imaging (MRI) scan. On the fourth day of data collection, and after 4 to 6 hours of fasting and 48 hours of rest, participants underwent skeletal muscle and abdominal and gluteal SAT biopsies. Accelerometers (ActiGraph and ActivPAL) were attached to the participants and worn for 7 days.

**Figure 2 figure2:**
[figure not shown]
Schematic overview of testing timelines and procedures. VO2peak: peak oxygen consumption; STD: standard; DXA: dual-energy absorptiometry x-ray; RMR: resting metabolic rate, FSIGT: frequently sampled intravenous tolerance test; HR: heart rate; BP: blood pressure; FFQ: food frequency questionnaire; MRI: magnetic resonance imagery; SS: steady state treadmill test; %HRpeak: percent of peak HR.

Every 4 weeks following the start of the intervention, dietary intake (3-day dietary recall), physical activity and sleep quality and quantity (ActiGraph), and sedentary behavior (ActivPAL) were monitored. Following completion of the intervention, a subsample of women were invited to participate in focus group discussions and key informant interviews. Due to the large time commitments and travel requirements, participants were reimbursed at an hourly rate based on recommendations from the Health Sciences Human Research Ethics Committee of the University of Cape Town.

### 12-Week Exercise/Control Intervention

The exercise intervention consisted of 12-weeks of supervised aerobic and resistance training at a moderate-vigorous intensity for 40 to 60 min, 4 days per week by a trained facilitator. The exercise intervention was structured based on the results of a focus group study undertaken in the same community [34]. Exercises included cardiovascular exercises in the form of aerobic dance, running, skipping, and stepping that were performed at a moderate-vigorous intensity (75%-80% peak heart rate, HR_peak_). Resistance exercises included the participants using their own body weight and progressed to the use of equipment (eg bands and free weights). These exercises included squats, lunges, bicep curls, push-ups and shoulder press with a prescribed intensity of 60% to 70% HR_peak_. Attendance was recorded at each training session, and a heart rate monitor (Polar A300, Kempele, Finland) was worn by participants to ensure the prescribed exercise intensity was maintained throughout the 12-week period. Similarly, the respective resistance exercises were altered to ensure progression and to maintain the required intensity throughout the 12-week intervention. Training dose for the exercise group is calculated as the total number of sessions attended multiplied by the average percent of HR_peak_ attained over the 12-week period.

The control group was instructed to maintain their normal daily physical activity patterns, and not start any exercise training, which was verified through monthly monitoring using accelerometry. Following posttesting, the control participants were given the opportunity to participate in the 12-week exercise program, for which they were also reimbursed for their time and travel costs.

### Pre- and Postintervention Testing

#### Sociodemographic and Basic Health Information

The participants completed a demographic questionnaire that included measures of socioeconomic status (on the basis of factors such as asset index, education, housing and housing density, employment, and income) [35], family history of disease, personal health, reproductive history, supplement use, body image [36], alcohol use, and household food security [37]. In addition, measures of psychological well-being, including the Pittsburgh Sleep Quality Index [38], Beck Depression Inventory [39], the Kessler 10 [40], and the General Self-Efficacy [41] Questionnaires, were administered.

#### Body Composition Assessment

Basic anthropometry, including weight and height, in lightweight clothing without shoes, as well as waist circumference at the level of umbilicus, and hip circumference at the largest protrusion of the buttocks, were measured to the nearest 0.1 cm. Whole body composition, including fat mass and fat-free soft tissue mass (FFSTM), were measured by DXA (Discovery-W, software version 12.7.3.7; Hologic, Bedford, MA) according to standard procedures, with a coefficient of variation of 0.7% for FFSTM and 1.67% for fat mass. Subtotal (excluding the head) fat and FFSTM were used for all analyses. Regional body fat distribution, including arm, leg, trunk, gynoid, and android fat mass, was characterized as previously described [42] and abdominal VAT and SAT areas estimated [43].

#### Cardiorespiratory Fitness

To determine cardiorespiratory fitness, VO_2peak_ was measured using a treadmill-based (C, Quasar LE500CE, HP Cosmos, Nussdorf-Traunstein, Germany) graded exercise test. Participants were familiarized to the equipment before beginning the test, and heart rate was monitored throughout for the determination of HR_peak_ (Polar A300, Kempele, Finland). The initial 6 min of the test was designed based on a modified Bruce protocol to obtain three stages of steady state metabolism (see steady state protocol below) and the subsequent minutes were designed to obtain VO_2peak_ using a ramp protocol, adapted from Takagi et al [44]. Participants began at 3 km/hour at a 2% gradient for 2 min. The gradient increased by 2% for a further two 2-min segments. The following stages increased by 2% gradient every minute until 16%. Following this there was an alternate increase in speed (0.5 km/hour) and gradient (1%) until volitional exhaustion. This walking cardiorespiratory fitness test was designed for participants who were sedentary and are not familiar with gym-based equipment.

Pulmonary gas exchange was measured by determining O_2_ and CO_2_ concentrations and ventilation to calculate VO_2_ consumption using a metabolic gas analysis system (CPET, Cosmed, Rome Italy). Before each test, the gas meter was calibrated with a Hans Rudolph 3-liter syringe (Vacumed, Ventura, CA) and analyzers calibrated using standard gas mixtures of oxygen (26% O_2_ with the balance nitrogen) and carbon dioxide (4% CO_2_, 16% O_2_, and the balance nitrogen) (BOC Special Gas, Afrox Cape Town, South Africa). Ethanol burns for equipment calibration were conducted every 4 weeks (mean variance<2%).

#### Energy Expenditure and Substrate Metabolism During Submaximal Steady-State Exercise

Following an overnight fast (10-12 hours) respiratory exchange (Cosmed Quark CPET, Rome, Italy) was measured during 15 min of steady-state treadmill walking at 50% VO_2peak_, a level shown to be consistent with maximal fat oxidation [45,46]. Measures of energy expenditure and substrate metabolism were averaged over the last 10 min of the test. This test (50% pre-intervention VO_2peak_) was repeated at posttesting, which reflects the same absolute intensity. Participants then rested for 10 min and completed a second steady-state exercise test, at 50% of the postintervention VO_2peak_, which reflects the same relative exercise intensity.

#### Resting Metabolic Rate, Substrate Metabolism, and Blood Pressure

Participants slept overnight at the laboratory and were given a standardized evening meal at 8 PM (Energy: 2,456 kJ, 21 g protein (14% energy), 49 g carbohydrate (33% energy), and 32 g fat (48% energy). At 6 AM (following a 10-hour overnight fast), the participants rested in the supine position, in a quiet room (21°C -24°C), and were instructed to remain awake, still, and quiet. Basal respiratory exchange was measured for 40 min, using the ventilated hood technique (CPET, Cosmed, Rome Italy). The first 10 min were excluded to ensure measures of steady state respiratory gas exchange and the average of the last 30 min was used to determine resting measures. Weir [47] and Frayn [48] equations were used to calculate RMR and total rates of fat and carbohydrate oxidation, respectively. During the respective 40 min, the lowest recorded heart rate was recorded and reported as the resting heart rate.

#### Fasting Blood Samples and Frequently Sampled Intravenous Glucose Tolerance Test (FSIGT)

Following the RMR measures, fasting blood samples were drawn, and an FSIGT was performed. A cannula was inserted into a vein of each arm. One arm was used for intravenous glucose and insulin infusions, and the other arm was heated and used for blood sampling. Fasting blood samples were drawn for the determination of adipokines, myokines, inflammatory markers and cytokines, lipid profiles and HDL- and LDL-cholesterol subtypes and HDL functionality, and red blood cell fatty acid composition, metabolomic and lipidomic analysis.

For the FSIGT, further 2 baseline samples were collected at −5 and −1 min before a bolus of glucose (50% dextrose; 11.4 g/m^2^ body surface area) was infused intravenously over 60 seconds beginning at time 0. At 20 min, human insulin (0.02 U/kg; NovoRapid, Novo Nordisk) was infused over 5 min at a constant rate (HK400 Hawkmed Syringe Pump, Shenzhen Hawk Medical Instrument Co., Shenzhen, China). Samples for determination of plasma glucose and serum insulin and c-peptide concentrations were drawn at 2, 3, 4, 5, 6, 8, 10, 12, 14, 16, 19, 22, 23, 24, 25, 27, 30, 35, 40, 50, 60, 70, 80, 90, 100, 120, 140, 160, 180, 200, 220, and 240 min.

Fasting blood samples were collected into EDTA, lithium heparin, fluoride oxalate, and SST tubes. Samples in SST tubes clotted for 30 min at room temperature, while the remaining samples were placed on ice before centrifugation. Samples were centrifuged at 3000 rpm for 10 min at 4°C. Plasma for glucose analysis was stored at −20°C, while the remaining serum and plasma was stored at −80°C. Red blood cells collected from EDTA tubes were washed by 2 cycles of sequential centrifugation at 1000 rpm and a final cycle of centrifugation at 3000 rpm for 10 min. Between cycles, saline (0.9% NaCl in distilled water) was used for resuspension and washing. Red blood cells were then stored at −80°C until the analysis.

Glucose and insulin concentrations from the FSIGT will be used to calculate the insulin sensitivity index (S_I_) using Bergman’s minimal model of glucose kinetics [49]. Glucose and c-peptide data will also be used in a two-compartment minimal model of C-peptide secretion and kinetics to calculate insulin secretion rate (ISR) using WinSAAM (version 3.3.0). ISR will then be used in a one-compartment insulin minimal model to determine insulin hepatic extraction index [50].

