### Aims and Objectives

The aim of the study was to identify mechanisms underlying the changes in insulin sensitivity and secretion in response to a 12-week aerobic exercise intervention in obese black SA women.

The objectives of the study were as follows:

to measure changes in insulin sensitivity and secretion (primary outcomes) in response to the 12-week intervention compared with the nonexercise control groupto measure changes in potential primary and secondary determinants (secondary outcomes) of insulin sensitivity and secretionto examine the associations between changes in insulin sensitivity and secretion and changes in the primary and secondary determinants

Primary determinants were as follows:

cardiorespiratory fitnessbody composition and body fat distributionblood pressurelipid profile, including high-density lipoprotein (HDL)- and low-density lipoprotein (LDL)-cholesterol subclasses and HDL functionalityectopic fat deposition (skeletal muscle, liver, and pancreas)skeletal muscle expression of genes and proteins involved in insulin signaling, oxidative capacity, and mitochondrial biogenesisskeletal muscle and serum metabolomics and lipidomic profilegluteal and abdominal subcutaneous adipose tissue expression of genes and proteins involved in inflammation, insulin signaling, oxidative stress, vascularization, adipogenesis, and lipid metabolismcirculating inflammatory cytokine, myokine, and adipokine concentrationsskeletal muscle and adipose tissue mitochondrial respiration and hydrogen peroxide production;gastrointestinal microbiota

Secondary determinants were as follows:

energy expenditure and substrate metabolism at rest and during exercisehabitual physical activity and sedentary behavior patternsdietary intake, red blood cell, and adipose tissue fatty acid compositionsleep quantity and qualitypsychological well-beingperceptions of body image, healthy behaviors, and the exercise intervention

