### Biochemical Analysis

#### Glucose, Insulin, C-Peptide, and Lipid Profile

Plasma glucose and serum lipids concentrations were determined using a colorimetric assay (Randox, Gauteng, South Africa) and serum insulin, C-peptide were measured using immunochemiluminometric assays (IMMULITE 1000 immunoassay system, Siemens Healthcare, Midrand, South Africa).

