### Statistics

#### Sample Size Determination

Sample size determination was based on our primary outcome using the study of Nordby et al [80], with a significance level of *P*<.05 and power of 80%. On the basis of the change in normalized glucose clearance (measured using a euglycemic hyperinsulinemic clamp) from pre- to postintervention (12-week aerobic training) compared with the nontrained control group (8.2 [SD 5.9] vs −1.8 [SD 6.2] mL/kg/min FFM/nmoL/L insulin, respectively), 6 participants per group would be required to detect a significant difference between groups. These numbers correspond to those of Ortega et al [81] who compared glucose tolerance tests to detect the insulin sensitizing effects of a bout of continuous exercise and reported that 6 participants would be required to detect a change in insulin sensitivity when using a FSIGT. In order to account for the secondary outcomes, using changes in skeletal muscle glucose transporter (GLUT)4 in response to a 12-week training program as the proxy (0.65 [SD 0.69] vs 0.01 [SD 0.69] AU for training vs control group), 18 women would be required to detect a difference between groups [81]. On the basis of these calculations, and a dropout rate of 10% (2/20), 20 participants per group were selected.

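### The FSIGT insulin is labelled human insulin but named as NovoRapid; if an analogue was infused, S_I depends on an assay recovery that should be confirmed before fitting

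*Protocol article*

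**What the plan says.** All places are in the protocol article.

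- **Product.** The section on fasting blood samples and the FSIGT states that at 20 min "human insulin (0.02 U/kg; NovoRapid, Novo Nordisk) was infused over 5 min at a constant rate". The generic label and the brand stand in the same parenthesis.
- **Assay.** Under Biochemical Analysis (Glucose, Insulin, C-Peptide, and Lipid Profile), "serum insulin, C-peptide were measured using immunochemiluminometric assays" on a single named platform, IMMULITE 1000. No figure is given for how fully it reads the infused product.
- **Sensitivity.** "Glucose and insulin concentrations from the FSIGT will be used to calculate the insulin sensitivity index" by the minimal model, so the measured insulin curve is a direct input to S_I.
- **Secretion.** "Glucose and c-peptide data will also be used in a two-compartment minimal model of C-peptide secretion and kinetics to calculate insulin secretion rate (ISR"). This does not use the insulin curve.
- **Status.** Aims and Objectives sets out "to measure changes in insulin sensitivity and secretion (primary outcomes"), and a further objective relates their changes to changes in the determinants. The assays are reported in the past tense and the modelling in the future tense. Study Design says analysis is ongoing.

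**The concern.** The minimal model takes the measured insulin curve to be the insulin acting on glucose. From 20 min that curve should contain both the woman's own insulin and the infused insulin. If the assay under-reads the infused part, glucose falls under insulin that the curve does not show, and the model attributes the extra fall to higher sensitivity.

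The error is not a fixed percentage. It grows with the ratio of infused to endogenous insulin, which differs between women and may differ between visits. S_I would then partly track endogenous insulin. That matters in a trial whose aim is mechanism: the change in S_I is compared between arms and is also correlated with changes in the determinants.

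**Working it through.** **The plan's own figure.** Sample Size Determination gives changes of 8.2 (SD 5.9) and −1.8 (SD 6.2), with "a significance level of *P*<.05" and 80% power. Pooled SD = √((5.9² + 6.2²)/2) = 6.05; difference = 10.0; n = 2 × (1.96 + 0.84)² × (6.05/10)² ≈ 5.7, so 6 per group, as stated. This point does not change that number.

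**The rise the infusion should produce.** The dose is 0.02 U/kg over 5 min, which is 4 mU/kg/min. With distribution volume V and elimination rate k (both assumed), the peak rise at 25 min is (4/V)/k × (1 − e^(−5k)).

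- V = 0.10 L/kg, k = 0.20/min: 40/0.20 × (1 − e^(−1.0)) = 200 × 0.632 ≈ 126 microU/mL.
- V = 0.15 L/kg, k = 0.15/min: 26.7/0.15 × (1 − e^(−0.75)) = 178 × 0.528 ≈ 94 microU/mL.

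At full recovery a rise of roughly 95–130 microU/mL should therefore be visible. Samples are scheduled at 19 min (before the infusion) and at 22, 23, 24, 25, 27 and 30 min.

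**Effect on S_I.** The model is dG/dt = −(SG + X)G + SG·Gb and dX/dt = −p2·X + p2·S_I·(insulin above basal). Glucose was simulated at the protocol's sampling times under endogenous plus infused insulin, with both acting equally unit for unit. S_I was then refitted, from 8 min onward, to endogenous + c × infused insulin, where c is the share the assay reads. All kinetic values and c are assumptions.

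- Set A: V 0.10 L/kg, k 0.20/min, SG 0.02, p2 0.03.
- Set B: V 0.13 L/kg, k 0.14/min, SG 0.018, p2 0.03; infused insulin about 22% of the incremental insulin AUC before training.

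True S_I is 2.0 before and 2.6 after (×10⁻⁴), a 30% rise, with endogenous insulin about 23% lower after training.

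| c | Fitted/true S_I before, A | Same, B | Apparent rise, A | Apparent rise, B |
|---|---|---|---|---|
| 1.0 | 1.00 | 1.00 | 30% | 30% |
| 0.8 | – | 1.05 | – | 32% |
| 0.5 | 1.29 | 1.14 | 33% | 35% |
| 0.2 | 1.44 | 1.24 | 37% | 40% |
| 0 | 1.50 | 1.33 | 41% | 43% |

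Example, set A at c = 0: S_I is fitted as 3.00 before and 4.22 after, and 4.22/3.00 = 1.41.

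With endogenous insulin unchanged, set B reads the 30% rise as 31%, 33%, 36% and 37% at c = 0.8, 0.5, 0.2 and 0.

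**Dependence on endogenous insulin.** In a low secretor under set B (infused share about 52%), fitted/true S_I is 1.24 at c = 0.8 and 1.96 at c = 0.5. Below that the fit is unstable and is not used.

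**The case against.** The strongest reply is that the article contains a naming mismatch and nothing more. That NovoRapid is an analogue comes from outside the document. The bias turns on a recovery figure that nobody reading the article has: the range includes zero, and nothing in the text makes low recovery likelier than full recovery. Recovery data may well sit in a full protocol or laboratory manual, so their absence from a condensed article is not a fault. Even at the extreme, a true 30% rise reads as 41–43%, with its direction unchanged.

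Most of this stands, and it makes the point conditional. What remains is that label and brand disagree in the text as printed, and that S_I as described would carry any under-recovery straight into a primary outcome and its correlations.

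A reader might infer more, without support:

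- **That both primary outcomes are affected.** Secretion is calculated from glucose and C-peptide, not from the insulin curve.
- **That the hepatic extraction index fails even at full recovery.** The article says "ISR will then be used in a one-compartment insulin minimal model to determine insulin hepatic extraction index". It does not say that ISR is the only input or that the infusion is left out.
- **That a large spurious training effect is to be expected.** Under set A at zero recovery, two profiles with the same true S_I, one with about half the endogenous insulin, read 5.0 and 3.0, a 67% difference. That needs both extremes at once. The article does not say that training will halve, or even lower, endogenous insulin; the Discussion anticipates only better sensitivity and lower diabetes risk.
- **That none of the error cancels.** It applies to both arms and both visits, and most of it drops out of relative change.

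**Conclusion.** The point holds in conditional form. The description of the infused insulin is inconsistent and must be reconciled. If the product was an analogue and the assay reads it incompletely, S_I is overstated: by 0% at full recovery, 14–29% at half recovery and 33–50% at none. A true 30% rise with falling endogenous insulin then reads as 33–35% at half recovery and 41–43% at none. These figures rest on assumed kinetics, equal action of infused and endogenous insulin, and an endogenous fall of about 23%. The documents cannot show whether any bias occurred. This is a cheap improvement to make before modelling, not an established error in the primary analysis.

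**What to change.** Before S_I is fitted:

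1. State which product was infused and correct whichever of the label or the brand is wrong.
2. Compare the existing 22–30 min insulin values with the 19 min value and look for the expected rise (about 95–130 microU/mL at full recovery under the assumed kinetics). This detects gross failure only.
3. Confirm the assay's recovery of that product from the assay documentation or a small spike-recovery run, and report it.
4. If recovery is incomplete, correct the insulin input for the known infusion, or report S_I with that correction as a sensitivity analysis. Re-assay only if residual FSIGT serum exists; the storage paragraph opens with the fasting samples and does not settle this.

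Steps 1 and 2 cost almost nothing. Step 3 is a small laboratory check. Step 4 adds some modelling and arises only if recovery falls short.
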